#### **2.3.8.1.4. Final dataset for case-control study**

We will disaggregate the editorial decision variables from the submission data so that determination of author's gender and all other data extraction will be done blinded to editorial decision. Finally, for analysis we will combine the separate databases using the manuscript identity number.

### **2.3.9. Statistical methods**

#### **2.3.9.1. Sample size**

As described above, we will consider an odds ratio of 0.85 for the acceptance for publication by first-author gender (0.85 for women versus men), to indicate the presence of gender bias. We assume a proportion of women first authors of 40% among cases and 44% among controls using  $OR=0.85$ . Taking into account a type-1 error at 5% (two-sided) with a study power of 90% and a correlation coefficient for exposure between matched controls and cases at 0.03 (to take into account some clustering at the journal level), this would require 2800 articles accepted and 2800 articles rejected after peer review. To take into account at least 20% of missing values among modelled variables, we will select a total of 3500 accepted and 3500 rejected manuscripts. We will randomly select an

equal number of articles per journal-year (20 cases and 20 controls) corresponding to a maximum of 160 cases and 160 controls for each journal. Currently, 23 journals have agreed to participate.

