#### **2.3.8.1.3. Identification of authors' gender**

The identification of first, corresponding and last author's gender will be performed independently of the editorial decision (accepted or rejected for publication) via an internet search using specific tools by a collaborator in the research team. This will be performed separately for the case-control study and for the retrospective cohort study. Determination of authors' gender will be based on first name, middle name, salutation and the country of the author's affiliation. We will use binary gender identification that will not be based on the self-reported gender identity. We will determine gender by using a sequential four step procedure. Firstly, we will use both first name and country to search in the Gender API (<https://gender-api.com/en>) website. Gender API provides gender determination with an accuracy probability from 50% to 100% (under 50% an unknown status is attributed), gives the number of samples retrieved to search for the information, ensures that the level of misclassification is around 5%, and has the highest coverage on the variability in name origins. We will set gender accuracy above 60% as the minimum criterion for inclusion in the primary gender determination. Secondly, for all authors with undetermined or unknown gender based on the above, we will use the authors' given middle names and country to search in Gender API. Thirdly, we will use the online service genderize.io (<http://genderize.io>) to determine gender on the basis of first names and middle names, also using an accuracy above 80% as the minimum criterion. Fourthly, for still undetermined gender, we will use the authors' title/salutation and attribute it male gender to "Mr" or "M" and female gender to "Miss," "Mrs," and "Ms." Where none of these methods determine the gender, we will record the gender as undetermined.

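### The 2800 articles per group said to give 90% power give about 84–87% on the protocol's own inputs; 90% needs about 3100–3370 per group

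*Protocol*

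**What the plan says.** Section 2.3.9.1 gives every input. The target is an odds ratio of 0.85 for acceptance, women versus men first authors. On exposure it says "We assume a proportion of women first authors of 40% among cases and 44% among controls". The test is two-sided at 5%, with 90% power. It adds "a correlation coefficient for exposure between matched controls and cases at 0.03", explained as an allowance for some clustering by journal. From these it concludes that "this would require 2800 articles accepted and 2800 articles rejected after peer review".

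It then raises the number to 3500 per group because at least 20% of values in the modelled variables may be missing. Since 2800 / 0.8 = 3500, the figure of 2800 is the analysable number and the extra 700 is already spoken for.

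The section does not name a formula. It does not say whether 0.85 is a marginal odds ratio or one conditional on the matching.

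**The concern.** When all inputs are printed, a reader should be able to recover the sample size to within rounding. Here the usual formulas return figures 11–20% above 2800.

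This bears on the primary objective, because the protocol plans to interpret a null result. Section 1.4 says that if no gender bias is found, the imbalance is more likely to arise before the editorial decision, and section 2.5.2 expects other researchers to redirect effort on that basis. Anyone weighing such a null relies on the stated 10% chance of missing an odds ratio of 0.85.

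**Working it through.** **Inputs (all from section 2.3.9.1).** p1 = 0.40 (accepted), p0 = 0.44 (rejected), z = 1.960 for two-sided 5%, z = 1.2816 for 90% power, correlation φ = 0.03, n = 2800 per group. The proportions agree with the odds ratio: (0.40/0.60)/(0.44/0.56) = 0.8485.

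**1. Unmatched, two proportions.**
n = [1.960·√(2·0.42·0.58) + 1.2816·√(0.40·0.60 + 0.44·0.56)]² / 0.04² = (1.3680 + 0.8938)² / 0.0016 = 3197.4, so 3198.
Power at 2800: Φ[(√2800·0.04 − 1.3680)/√0.4864] = 85.8%.
With the odds ratio at exactly 0.85 (p1 = 0.4004): n = 3268, power 85.1%.

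**2. Matched pairs, stated proportions, φ = 0.03.**
c = 0.03·√(0.40·0.60·0.44·0.56) = 0.0073.
Discordant probabilities: 0.40·0.56 − c = 0.2167 and 0.60·0.44 − c = 0.2567. Their sum is 0.4734 and their difference is 0.04.
n = [1.960·√0.4734 + 1.2816·√(0.4734 − 0.0016)]² / 0.0016 = 3105.
Power at 2800: 86.8%.
At φ = 0 the same formula gives 3201, so here the correlation lowers the requirement.

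**3. Matched pairs, conditional odds ratio 0.85, φ = 0.03.**
The ratio of the discordant probabilities is set to 0.85 with p0 = 0.44, which gives p1 = 0.4016 and discordant probabilities 0.2176 and 0.2560. The formula of step 2 then gives n = 3371 and power at 2800 of 84.0%. A standard matched case-control formula gives 3367.
At φ = 0 the requirement is about 3270, so here the correlation raises it.

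| Reading | n per group for 90% | Power at 2800 |
|---|---|---|
| Unmatched, 40% vs 44% | 3198 | 85.8% |
| Matched, 40% vs 44%, φ = 0.03 | 3105 | 86.8% |
| Matched, marginal OR 0.85, φ = 0.03 | 3173 | 86.1% |
| Matched, conditional OR 0.85, φ = 0.03 | 3371 | 84.0% |

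**4. Effect detectable with 90% power at 2800.** The standard error of the log odds ratio is √[1/(2800·0.40) + 1/(2800·0.60) + 1/(2800·0.44) + 1/(2800·0.56)] = 0.0542, and exp[−(1.960 + 1.2816)·0.0542] = 0.839.

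**5. Attempts to recover 2800.** Two departures come within 3%: 85% power, two-sided, unmatched with odds ratio 0.85 (2793), and 90% power with a one-sided 5% test, matched with a conditional odds ratio (2743–2747). Each contradicts a stated input, so the document does not settle where 2800 came from.

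**6. Conditional note on gender coding.** Section 2.3.8.1.3 says of Gender API that it "ensures that the level of misclassification is around 5" per cent. Suppose the error is 5% in each direction and the same in both groups, and that the planning inputs refer to true gender. Then p becomes 0.95p + 0.05(1 − p): 0.40 becomes 0.410 and 0.44 becomes 0.446. The odds ratio becomes 0.863. Power at 2800 is 77.7% unmatched, 78.7% for matched pairs with the stated proportions, and 75.3% with the conditional odds ratio.

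**The case against.** Four objections deserve an answer.

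- **The gap is small and the margin may cover it.** If all 3500 per group were analysable, power would be about 91–93%. That is correct, but the protocol itself expects to lose at least 20%. Its count in section 2.3.8, 172 journal-years × 20 = 3440, leaves 2752 after that loss, slightly below 2800. That the shortfall is moderate stands.
- **Rounding of the inputs.** This does not close the gap: 90% at 2800 needs an odds ratio of about 0.84, and the stated proportions imply 0.8485.
- **Gender misclassification.** A reader might infer that true power is about 78%. The protocol does not support that as a plain statement. The 5% is given for one tool, not for the four-step procedure. Equal error in both directions is not stated. Nor is it stated that 40%, 44% and 0.85 refer to true rather than name-inferred gender; if they describe name-inferred gender, there is no further attenuation. Only equal error in the two groups has support, from the blinded coding in section 2.3.8.1.4. An added analysis restricted to high-accuracy names is not called for here either: it may sit in an analysis plan not at hand, and Appendix 7 lists no accuracy score.
- **The 0.03 correlation.** A reader might infer that it works against its stated purpose because it lowers the number in step 2. In step 3 it raises the number. The protocol does not say which reading applies, so the clustering explanation cannot be called wrong.

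**Conclusion.** The stated 90% power is wrong as written. On the protocol's own inputs, 2800 analysable articles per group give 84.0–86.8% power, and 90% needs 3105–3371 per group. The range reflects only the choice of formula and the meaning of 0.85; every two-sided 90% reading tried falls short. The loss is 3 to 6 points of power.

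This rests on the stated proportions and odds ratio, two-sided 5%, one control per case, and the 20% loss that the protocol allows for. The further fall to roughly 75–79% is a conditional remark and not part of the error.

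**What to change.** In section 2.3.9.1:

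- State that 2800 analysable articles per group give about 84–87% power for an odds ratio of 0.85, and 90% for about 0.84. Once the formula is fixed, give the single figure.
- Name the formula, and say whether 0.85 is a marginal or a conditional odds ratio. This also settles in which direction the 0.03 correlation acts.
- Optionally, note that if the planning values refer to true gender and coding error is about 5%, symmetric and unrelated to the decision, the observable odds ratio is about 0.86 and power roughly 75–79%.

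The cost is a few sentences. The number of manuscripts, the data collection and the primary analysis do not change. Keeping the 90% claim instead would need about 3880–4215 selected per group (3105 / 0.8 to 3371 / 0.8) against the 3500 planned.

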
results. We recently reported a double gender and geographical bias in the invitation and participation to the peer review process. Women are less invited to peer review (39% women among invited peer reviewers) compounded by fewer women agreeing to peer review invitations (31% women agreed vs. 38% of men). Reviewers with African, Asian and South American affiliations and those from low- and middle-income countries are underrepresented, even when they were more likely to agree to review.

With regards to the division of labour in research, similar to the findings from other studies, our analysis of published article contribution statements found there are significant differences between men and women authors: men are more frequently assigned tasks considered more prestigious, such as conception and study design, fundraising, data analysis, and paper writing, while women are assigned more operational tasks such as data collection, logistics and administrative support. These differences could explain why women are less likely to be last author compared to men as reported elsewhere. Women were more frequently second authors and less likely next-to-last authors compared to men. Some characteristics of submitted manuscripts, such as study design, analytical methods, disclosure of funding source and country where the research took place were also independently associated with acceptance for publication. It is also possible that within research collaborations, women are frequently offered first or last authorship on secondary less important and lower-quality papers. If this were the case, we would expect to find that women are more frequently authoring papers of lower quality or that women are more frequently first authors of papers presenting results from ancillary or *post-hoc* studies. This would also explain why women have fewer publications and citation rates compared to men, and thus have lower h-indices.

While we have identified a gender gap generally in the research process, to our knowledge, no studies have yet explored specifically the existence of gender bias at the final stage of the publishing process: when the editor of a medical journal decides to accept or decline a submitted research manuscript. The existence of geographical and income-country bias has not been further investigated in the acceptance for publication.

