### 2.3.3. Objectives

Our **primary objective** is to evaluate the influence of first-author gender on acceptance rates of original articles submitted to leading medical journals that were sent for peer review.

Our **secondary objectives** are: 1) to study the influence of corresponding-author gender and last-author gender on acceptance for publication; 2) to test whether the editor's or associate editor's (see glossary) gender modifies the influence of author gender on acceptance for publication; 3) to determine whether the influence of author gender on acceptance for publication varies over an eight-year period; 4) to determine the proportion of women first authors at each stage of the editorial decision-making process; 5) to possibly explore whether the reasons for manuscript rejection differ between women and men first, last and corresponding authors.

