#### **2.3.9.2. Statistical analyses**

Statistical analyses will be done by the postdoctorate under the supervision of [name]. We will present descriptive statistics for the proportions of women first authors that were: rejected without external review; sent for external peer review; rejected, accepted or invited to revise a manuscript after external peer review; and rejected and accepted after revision. To take into account clustering at the journal level, we will perform mixed-effects logistic regression to model the influence of the first author's gender on the odds of acceptance for publication, after adjustment for the confounders and covariates (cf. appendix 7) and using the journal as a random effect. We will perform the same logistic regression model to answer our secondary objectives to study the influence of corresponding-author gender or last-author gender on the acceptance for publication. To test whether the handling editor's gender or reviewers' gender modifies the association between first-author gender and the acceptance rate, we will include an interaction term between these two predictors. We will also test interactions of first author gender, respectively with the scope of the journal and with time on a yearly scale. Journals will be anonymised, therefore separate journal effects will not be presented when we publish the results but we will provide journal level data to individual journals upon request.

In the retrospective cohort, we will describe and compare, using Chi-2 tests, the proportion of women first authors for articles at the following points in the decision-making process: rejection without review; sent for peer review; rejected, accepted and sent for revision after peer review; and between articles rejected at any stage versus articles accepted for publication. To test whether the reasons for rejection mentioned in decision letters varies between men and women first (then corresponding and last) authors, we will include an interaction term between these two predictors in a mixed-effects logistic regression model with rejection as the dependent variable and journal as the random factor. All analyses will be performed using STATA 17.0 IC (StataCorp LP, College Station, TX, USA) and R software (version 4.0.5).

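### The sample-size allowance implies dropping articles with a missing covariate from the primary model, leaving about 85-86% power on the protocol's inputs; keeping them could give up to about 92%

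*Protocol*

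**What the plan says.** Section 2.3.9.1 fixes the target effect ("we will consider an odds ratio of 0.85 for the acceptance for publication by first-author gender"), the exposure rates ("We assume a proportion of women first authors of 40% among cases and 44% among controls"), the error rates ("Taking into account a type-1 error at 5% (two-sided) with a study power of 90" per cent) and "a correlation coefficient for exposure between matched controls and cases at 0.03". It arrives at 2800 accepted and 2800 rejected articles, then moves to 3500 of each "To take into account at least 20% of missing values among modelled variables".

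Section 2.3.9.2 gives the primary analysis as one mixed-effects logistic regression, "after adjustment for the confounders and covariates (cf. appendix 7) and using the journal as a random effect". It does not say what happens to an article with a missing covariate.

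Three other places bear on the point:
- The primary objective in 2.3.3 is "to evaluate the influence of first-author gender on acceptance rates of original articles submitted to leading medical journals that were sent for peer review". It is not limited to fully reported papers.
- The editorial decision defines cases and controls (2.3.7.1), and articles whose first-author gender cannot be identified are excluded (2.3.5.2).
- In Appendix 7, significance of the main results has codes for unknown and not applicable, and funding disclosure has one for not mentioned. Effective sample size, number of centres, first author's degrees and handling editor's gender have no such code.

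**The concern.** Dividing by 0.80 makes sense only if an article with a missing model variable contributes nothing to the primary analysis. For an eligible article that is wasteful. Its exposure and outcome are already in hand, and what is missing is a variable used for adjustment. Deleting the whole row discards gender and decision data to avoid a gap elsewhere.

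Two things are at stake. The first is precision: up to a fifth of the collected articles, in a study looking for an odds ratio as close to 1 as 0.85. The second is the population to which the odds ratio applies. Section 2.1 reports that features such as "disclosure of funding source and country where the research took place were also independently associated with acceptance for publication", and it raises the possibility that women more often lead lower-quality papers. If how fully a paper reports its attributes went with both the decision and the author's gender, an analysis of complete articles would not estimate what the objective asks for.

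**Working it through.** **The inflation.** 2800/(1 - 0.20) = 3500, which reproduces the protocol's figure exactly. The alternative 2800 x 1.20 would give 3360. The number meant to remain for analysis is therefore 2800 per group.

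**Power at 2800 and 3500.** Inputs from 2.3.9.1: p1 = 0.40 (cases), p0 = 0.44 (controls), two-sided 5%. The comparison is unadjusted and unmatched, with n per group and pooled variance under the null:

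z = [|p1 - p0| x sqrt(n) - 1.96 x sqrt(2 x 0.42 x 0.58)] / sqrt(0.40 x 0.60 + 0.44 x 0.56)

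The null term is 1.96 x 0.698 = 1.368 and the denominator is 0.697.
- n = 2800: (2.117 - 1.368)/0.697 = 1.07, power 85.8%.
- n = 3500: (2.366 - 1.368)/0.697 = 1.43, power 92.4%.

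An odds ratio of exactly 0.85 implies p1 = 0.4004, and power is then 85.1% and 91.8%.

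**Number needed for 90%.** The same formula solved for n gives 3198 per group (40% v 44%), or 3268 (odds ratio exactly 0.85). A matched case-control formula with correlation 0.03 gives 3295 to 3367. Reading the correlation as a 3% saving gives 3102 to 3170. None reproduces 2800, which corresponds to about 85% power (2733 to 2793).

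**Standard error of the log odds ratio.** SE = sqrt[(1/0.40 + 1/0.60 + 1/0.44 + 1/0.56)/n] = 0.0542 at 2800 and 0.0485 at 3500, a ratio of 1.118. Around an odds ratio of 0.85 the 95% interval is about 0.76-0.95 against 0.77-0.93.

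**Articles available.** Section 2.3.8 counts 172 journal-years with 20 cases each: 172 x 20 = 3440 per group, not 3500. Keeping all of them gives 92.0% power; losing 20% leaves 2752 and 85.2%.

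**Losses above 20%.** The protocol's allowance is a minimum, but the inflation covers exactly 20%. Starting from 3500 per group:

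| Missing | Left per group | Power |
|---|---|---|
| 20% | 2800 | 85.8% |
| 25% | 2625 | 83.6% |
| 30% | 2450 | 81.0% |
| 40% | 2100 | 74.8% |

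**Bias.** If a share r of articles is complete in each gender-by-decision cell, the crude complete-case log odds ratio shifts by

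ln[(r women cases x r men controls)/(r men cases x r women controls)].

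Retention that differs only by decision, or only by gender, cancels. Joint variation does not. The protocol gives no retention by cell, so the following is an assumption: 80% complete in three cells and a different share in the fourth. A fourth cell at 82% shifts the log odds ratio by ln(0.82/0.80) = 0.025, which is 15% of |ln 0.85| = 0.163. At 85% the shift is 0.061, or 37%. The direction depends on which cell differs.

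**The case against.** The strongest objection is that the protocol nowhere announces a complete-case analysis. Inflating a sample size is a precaution, and the missing-data method may sit in an analysis plan that is not at hand. This stands as far as it goes: a reader might infer that row deletion is the stated plan, but it is only implied. The point survives because the sample-size section itself commits to a calculation that has no other natural reading, and the analysis section names nothing that departs from it.

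Further objections also limit the claim:
- **Loss against the plan.** At exactly 20% missing, the intended 2800 remain. The loss is relative to the articles collected. A reader might blame missing data for the shortfall from 90%, but it arises because 2800 is too small for the stated inputs.
- **Not all sampled articles need have a known gender.** Section 2.3.8 describes no gender screen before the draw, and 2.3.8.1.3 allows an undetermined result. Part of the 20% may be such articles, which are excluded and which covariate imputation cannot recover.
- **Some gaps are not gaps.** Where Appendix 7 has a code for unknown, not applicable or not mentioned, the article can stay in the model. Funding disclosure is one such variable.
- **Source of the data.** Section 2.3.8.1.1 takes author and editor data from the journals, so first author's degree and editor's gender are not subject to text-mining failure.
- **Bias is not shown.** Section 2.1 links manuscript features to acceptance; it does not link missing covariates to gender and decision together. Extraction blinded to the decision (2.3.8.1.4) limits differential extraction, though not differential reporting by authors.

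**Conclusion.** The point holds in a limited form and should be acted on. The sample size implies that articles lacking an adjustment covariate leave the primary model, although their decision and, once eligible, their first-author gender are known. The 2800 per group left would have about 85-86% power rather than the stated 90%. Retaining all sampled eligible articles could lift this to at most about 92%. That ceiling assumes 3440 to 3500 eligible articles per group and almost no information lost through imputation. It falls if some of the 20% are gender-undetermined or if many covariates must be imputed. All these figures are unadjusted and use the protocol's exposure rates.

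A reader might go further and conclude that the primary odds ratio will be biased. The document does not support that. Bias needs completeness to vary jointly with gender and decision, and no figures on this are given, so it remains a possibility and not a demonstrated error.

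**What to change.** In 2.3.9.2, state that:
- every sampled eligible article with known decision and first-author gender enters the primary model;
- missing covariates are multiply imputed, with decision, first-author gender, journal and submission year in the imputation model;
- the existing codes for unknown, not applicable and not mentioned are kept as categories where they describe a real state;
- the complete-case model is reported as a sensitivity analysis, and completeness is tabulated by gender and decision.

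In 2.3.9.1, restate power for the number of articles expected to be analysed: about 85-86% at 2800 per group, up to about 92% if all are retained. Separate the allowance for undetermined gender from the allowance for missing covariates.

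The cost is wording and some extra analysis work in software already named, with no further manuscripts. The downside is a missing-at-random assumption for the covariates. The complete-case sensitivity analysis and the completeness table help readers judge it but cannot prove it.

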#### **2.3.8.1.2. Extraction for the retrospective cohort study**

Regarding variables for the retrospective cohort, most variables will be directly exported from the journal systems in plain text (CSV or XLS). These variables will include the date of submission, the article's first decision and last decision, the authors' the countries of affiliation, and the journal identifier (case report form; see appendix 8). We will complete data extraction (for study design, statistical significance of main result, etc.) from the abstracts of the manuscripts by using text mining techniques elaborated by our project partner.

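### The cohort holds first-author gender and decision for every peer-reviewed article, but beyond the 20+20 sample these feed only unadjusted Chi-2 tests; add a journal-stratified cohort model as a supportive estimate

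*Protocol*

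**What the plan says.** **Primary estimate.** Sections 2.3.8 and 2.3.9.1 draw an "equal number of articles per journal-year (20 cases and 20 controls) corresponding to a maximum of 160 cases and 160 controls for each journal". On this sample, section 2.3.9.2 states: "we will perform mixed-effects logistic regression to model the influence of the first author's gender on the odds of acceptance for publication", with journal as a random effect and adjustment for the Appendix 7 covariates. Two reasons for sampling can be read from the text: acceptance is low in some journals (2.3.4), and PDFs are retrieved only for selected articles (2.3.8).

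**What is obtained for the whole cohort.**
- Outcome: section 2.3.8 asks each journal to list all 2012–2019 manuscripts with peer-review status and final decision. Appendix 8 codes rejection after review separately from acceptance.
- Exposure: on gender identification, section 2.3.8.1.3 says "This will be performed separately for the case-control study and for the retrospective cohort study". First-author gender is a field in Appendix 8.
- Covariates: section 2.3.8.1.2 exports "the date of submission, the article's first decision and last decision, the authors' the countries of affiliation, and the journal identifier" and mines further items from abstracts. Appendix 8 lists design, sample size, significance, funding, centres, number of authors and reviewer items.

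**What is done with the cohort.** Section 2.3.9.2 compares the share of women first authors at successive decision points, including rejected against accepted after review, by Chi-2 tests.

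**The concern.** The costly items are those that need the PDF. Gender, decision, journal and date are not among them, and most other covariates are also planned from abstracts. The 20+20 quota is therefore a sensible way to buy full-text covariates. It is not a reason to leave the remaining reviewed articles without a modelled estimate. Low acceptance in some journals is a reason to sample controls; it does not explain capping accepted articles at 20 where more exist.

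Two things are at stake. First, the gender odds ratio could be known more precisely from data already planned. That matters because section 1.4 would read a null result as pointing to discrimination upstream of the editorial decision, a conclusion that needs a narrow interval. Second, the cohort comparison as planned pools journals that may differ both in acceptance after review and in their share of women first authors. Section 2.3.9.2 itself says that clustering by journal must be taken into account, but does so only for the regression models.

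**Working it through.** **Inputs from the protocol.** 172 journal-years (2.3.8); 20+20 per journal-year; 40% women among cases and 44% among controls (2.3.9.1), which gives an odds ratio of (0.40×0.56)/(0.60×0.44) = 0.848.

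**Inputs assumed, because the protocol does not give them.** Reviewed articles per journal-year: 40, 60, 100 or 200. Share accepted after review: 41%.

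**Step 1, the plan's own counts.** 2800/0.80 = 3500 per group, as stated. The quota gives 172×20 = 3440 per group. (The 2800 itself does not reproduce: the pooled two-proportion formula for 40% against 44% at 90% power, two-sided 5%, gives 3198. That is a separate matter and is not used here.)

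**Step 2, precision of the planned sample (crude, no clustering).**
SE(log OR) = √[1/(n₁p₁q₁) + 1/(n₀p₀q₀)] = √[1/(3440×0.40×0.60) + 1/(3440×0.44×0.56)] = 0.0489. The 95% interval around 0.85 is 0.85×exp(±1.96×0.0489) = 0.77 to 0.94.

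**Step 3, the same formula on all reviewed articles.**

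| Reviewed per journal-year | Accepted + rejected | SE | Ratio to 0.0489 | 95% interval around 0.85 |
|---|---|---|---|---|
| 60 | 4231 + 6089 | 0.0406 | 0.83 | 0.78–0.92 |
| 100 | 7052 + 10,148 | 0.0315 | 0.64 | 0.80–0.90 |
| 200 | 14,104 + 20,296 | 0.0223 | 0.46 | 0.81–0.89 |

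At 40 reviewed, 41% is 16.4 accepted and 23.6 rejected. The quota takes nearly all of them, so there is no gain. The accepted share matters less than the pool: at 13,760 reviewed articles (twice the sampled 6880), shares of 30% to 50% give an SE of 0.035 to 0.038.

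These ratios are best cases, because they carry no cost for covariates that need the PDF.

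**Step 4, bringing in the PDF-only covariates.** A simple two-phase estimate is: unadjusted gender coefficient in the full pool + (adjusted − unadjusted coefficient in the 20+20 sample). It was simulated with 172 journal-years, a common true odds ratio of 0.85 and three PDF-only covariates (log odds ratios 0.3–0.5 per SD, differing by 0.1–0.2 SD between women and men). SE ratios across repeated simulations were 0.82–0.86 at 60 reviewed, 0.67–0.75 at 100 and 0.53–0.58 at 200. The lowest values partly reflect noise in the denominator. In one set the case-control SD ran from 0.050 to 0.056, although it should not depend on pool size; with 0.053 throughout, 0.036/0.053 = 0.68 and 0.030/0.053 = 0.57. Allowing for this, fair round figures are 0.8–0.9, 0.7–0.75 and 0.55–0.6. Mean log odds ratios were about −0.16 against ln 0.85 = −0.1625, so no bias appeared under a common effect.

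Scaling the crude SE of Step 2 by 0.75 gives 0.0367 and an interval of 0.79 to 0.91; by 0.60 it gives 0.0293 and 0.80 to 0.90.

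**Step 5, journal in the two analyses.** With filled quotas, the case-control sample has equal numbers accepted and rejected in every journal-year, so journal is balanced against outcome by design, and the model adds a journal effect. The cohort Chi-2 test has neither protection.

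**The case against.** A nested case-control sample with full-text covariates is a standard and stated choice, and extra cohort models are often left to the SAP, which is not shown. That stands for the primary analysis. It does not cover the cohort comparison, for which the protocol itself fixes a Chi-2 test without journal.

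A reader might infer that the unsampled reviewed articles are discarded, or that the primary odds ratio is biased. The documents support neither. The Chi-2 tests use those articles, section 2.3.7.1 makes cohort acceptance by author gender a secondary outcome, and random sampling within journal-year does not bias the primary estimate.

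A reader might also conclude that the cohort or two-phase estimate should replace the primary one. Three objections to that hold:
- **Weights.** Equal quotas weight journals by years; the pooled cohort weights them by volume. Appendix 2 mixes open, single-, double- and triple-anonymised review, so the effect may differ by journal. Suppose 22 journals review 60 articles a year with odds ratio 0.85, and one reviews 2000 with odds ratio 1.0. Equal weighting gives exp(22/23 × ln 0.85) = 0.86; volume weighting gives exp(1320/3320 × ln 0.85) = 0.94.
- **Population.** Section 2.3.5.2 limits the case-control study to clinical or translational work, while the cohort takes all original research and systematic reviews.
- **Availability.** Section 2.2 reports full submission data received from 11 journals only, and handling-editor gender is in Appendix 7 but not in Appendix 8.

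**Conclusion.** The point holds as one of efficiency and of an under-specified cohort analysis. The primary odds ratio uses at most 3440 + 3440 articles, while exposure, outcome, journal, date and most covariates are planned for every reviewed article, and the matching cohort comparison is unadjusted and ignores journal.

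The gain has no single size. It is nil at about 40 reviewed articles per journal-year and could roughly halve the standard error at 200. These figures rest on an assumed pool size, accepted share and covariate effects, on a common gender effect across journals, and on no missing data, although section 2.3.9.1 expects at least 20% missing among modelled variables. They show direction and range only. They justify a supportive estimate beside the primary one, not a change of primary analysis.

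**What to change.** Keep the case-control model as primary. In 2.3.9.2:

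1. Replace or supplement the cohort Chi-2 test of accepted against rejected after review with a logistic model of acceptance on first-author gender. Fit it in all peer-reviewed cohort articles that meet the eligibility rules of 2.3.5.2, conditional on or stratified by journal-year and adjusted for the Appendix 8 covariates. Pre-specify it as a co-reported supportive estimate.
2. Optionally add a two-phase estimate that brings in the PDF-only covariates from the nested sample, with a bootstrap interval drawn within journal-year.
3. Report how the gender effect varies across journals, using coded journals as 2.3.10 requires, and say whether the cohort estimate is weighted by volume or reweighted to equal journals.
4. In 2.3.8.1.3, determine gender once on the cohort file and carry it into the nested sample, so that an article cannot be classified differently in the two studies.
5. State the number of reviewed articles per journal-year once the lists are in hand.

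The cost is protocol wording and programming on data already planned. There are three small downsides: eligibility must be judged from article type and abstract, the weighting must be explained, and the editor-gender interaction stays within the case-control sample unless that field is added to Appendix 8.
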